## Abstract

**Background:**

Depression following acute coronary syndrome (ACS) constitutes a serious and debilitating problem. Approximately one in five patients will develop significant depression following ACS and less severe depressive symptoms are even more frequent. Furthermore, anxiety symptoms and sleep-wake disturbances are frequent. The objective of the MEDACIS trial is to investigate whether prophylactic treatment with melatonin has a preventive effect on depression, depressive and anxiety symptoms, sleep, and circadian disturbances following ACS.

**Methods/design:**

“The effect of MElatonin and Depressive symptoms, Anxiety, CIrcadian and Sleep disturbances in patients after acute coronary syndrome” trial (MEDACIS) is a multicenter, double-blinded, placebo-controlled, randomized clinical trial. A total of 240 patients with ACS and no depressive symptoms will be included in the trial for treatment with either 25 mg melatonin or placebo for a 12-week period. Development and severity of depressive symptoms will be evaluated using Major Depression Inventory every 2 weeks with the purpose of investigating the potential preventive effect of melatonin on depressive symptoms.

**Discussion:**

Previously, only selective serotonin reuptake inhibitors (SSRIs) have been investigated in a primary preventive setup in patients following ACS. However, SSRIs are associated with several side effects. An ideal intervention would constitute the highest degree of prevention of depressive symptoms with the lowest risk of side effects. In this regard, melatonin may have advantages due to its low toxicity as well as its proven anxiolytic and hypnotic effects.

**Trial registration:**

ClinicalTrials.gov, Identifier: NCT02451293. Registered on 12 May 2015. EudraCT nr. 2015-002116-32.

**Electronic supplementary material:**

The online version of this article (doi:10.1186/s13063-017-1806-x) contains supplementary material, which is available to authorized users.

## Background

By the year 2030 it has been anticipated that depressive disorder and ischemic heart disease will be the first and second leading causes of disability in developed nations, respectively [1]. Worldwide, an estimated 7 million people or more each year suffer from myocardial infarction (MI) [2]. In Denmark in 2011, the incidence rate of acute myocardial infarction was 553 cases/100,000 person-years, a prevalence of 4570 cases/100,000 persons, and a mortality of 123 cases/100,000 persons [3]. The prevalence of major depressive disorder following acute coronary syndrome (ACS) has been reported to be approximately 19.8% ((CI) 19.1% to 20.6%) assessed by structured clinical interviews [4]. However, the prevalence varies according to the tool used to evaluate depression [4–6], e.g., if the most frequently used self-report instrument, the Beck Depression Inventory (BDI), is used the prevalence is 31.1% ((CI) 29.2% to 33.0%) [4]. However, a prevalence as high as 50.5% has been reported with other questionnaires [5].

Depression following ACS has been associated with a 2.25 ((odds ratio), CI 1.73 to 2.93) increase in all-cause mortality, and a 2.71 ((odds ratio), CI 1.68 to 4.36) increase in cardiac mortality within 24 months of the primary event [7]. Depression was recently categorized by the American Heart Association (AHA) as an independent risk factor for adverse medical outcomes in patients after ACS [6]. Furthermore, the AHA has made recommendations for implementing screening for depression in the post-MI period [8].

Anxiety symptoms following ACS have not received as much attention as post-ACS depression [9]. A mix of both depressive and anxiety symptoms tend to coexist in patients following ACS [10] and they are found in up to 90% of depressed patients following MI [11]. The prevalence of anxiety symptoms varies from 24 to 37% among hospitalized MI patients [12, 13], and has been found to be associated with a 1.47-fold ((odds ratio), CI 1.02 to 2.13) increase in all-cause mortality [14]. However, a more recent meta-analysis could not confirm [15] this in post-ACS patients and the relationship was thought to be attenuated by comorbid depression. Anxiety symptoms have been shown to reduce heart rate variability [16], activate the hypothalamic-pituitary-adrenal axis [17], and enhance fibrin turnover [18]. Furthermore, anxiety is an independent predictor of cardiac events following MI [11, 19].

Sleep disturbances are prevalent in cardiac patients [20] and sleep disturbances are an integral part of both depression and anxiety symptoms [21]. In fact, in relation to the pathophysiology of depressive disorders, sleep and sleep-wake disturbances have been identified as two of the most important contributing factors [22]. The prevalence of sleep disturbances in ACS patients has not received sufficient attention [20], and the primary focus of the medical literature has been on sleep apnea, because of the known relationship between sleep-disordered breathing and cardiovascular morbidity [23]. This lack of relevant medical literature is disturbing, especially seen in the light of poor sleep having been shown to be associated with a 2.5-fold increased risk of recurrent cardiac events in women after ACS [24].

There exists a complex relationship between depression, sleep and circadian disturbances [25], and residual sleep disturbances may remain despite treatment of depression [26]. Furthermore, cognitive behavioural therapy (CBT) and pharmacotherapy have been shown to be equally effective in treating sleep disturbances after remission from depression [26]. Both psychological and pharmacological interventions could potentially be warranted in patients suffering from both medical illness and depression [27]. As oppose to antidepressants, psychotherapy has been shown to have a small but significant effect in the prevention of depression after stroke [28]. However, a limitation of psychological interventions is that the therapist and patient cannot be blinded to allocation which increases the risk of bias. An intervention where blinding is possible and which can target both the depression and the anxiety as well as the circadian and sleep disturbances in patients after ACS would be of clinical interest.

One possible pharmacological intervention investigated in the current trial could be the endogenous hormone melatonin (ATC: N05CH01). Melatonin is secreted from the pineal gland in a circadian pattern, controlled by the endogenous circadian pacemaker in the suprachiasmatic nuclei [29]. The primary function of melatonin is to synchronize the circadian rhythm of the body [29]. However, melatonin is a multipotent hormone and affects multiple processes in the human body [30–36] (Fig. 1). It has been shown to prevent depressive symptoms over a 3-month period in patients with breast cancer [37]. In the same population, it was shown to improve sleep quantity and quality both during a 2-week and a longer-term period (3 months) [38, 39]. Meta-analyses have shown melatonin to be effective in the treatment of primary sleep disorder [40]; however, the effect in secondary sleep disorders is limited [41]. In a perioperative setting, melatonin treatment has been shown to have an anxiolytic effect [42]. Choosing the ideal dose of melatonin regarding its antidepressant effect is difficult as no ideal dose-response studies have been carried out on this indication. Typically, melatonin is administered in under 10-mg doses [43] which is the dose used for treatment of insomnia in patients aged over 55 years [44]. The melatonin agonist agomelatine is on the market for the treatment of depression, and choosing an equipotent dose of melatonin to this agonist has been suggested [30]. The pharmacodynamics and pharmacokinetics of agomelatine and melatonin are similar [30] and the induction dose of agomelatine is 25 mg. A dose of 25 mg was chosen in the current trial as a balance between the primary prophylaxis (treatment before incident disease) design and the nontoxic profile of melatonin [40, 41, 45].

**Fig. 1 Fig1:**
[figure not shown]
MElatonin on Depressive symptoms, Anxiety, CIrcadian and Sleep disturbances (MEDACIS) trial. Potential effects of exogenous melatonin intervention

### Aim

The primary aim of the current study is to investigate a possible prophylactic antidepressant effect of melatonin in patients following ACS. Secondary aims will be to investigate whether melatonin will have effect on anxiety symptoms, sleep disturbances and circadian rhythm.

## Methods/design

The MEDACIS trial is a multicenter, double-blinded, placebo-controlled, randomized clinical trial investigating the effect of 25 mg exogenous melatonin (intervention group) against placebo (control group) and the study is designed as a parallel-group trial. The participants will be followed for a period of 12 weeks during the trial and assessed on outcomes continuously throughout the period (Figs. 2 and 3).

**Fig. 2 Fig2:**
[figure not shown]
MElatonin on Depressive symptoms, Anxiety, CIrcadian and Sleep disturbances (MEDACIS) CONSORT diagram. Consolidated Standards of Reporting Trials (CONSORT) diagram for the MEDACIS trial

**Fig. 3 Fig3:**
[figure not shown]
MElatonin on Depressive symptoms, Anxiety, CIrcadian and Sleep disturbances (MEDACIS) Standard Protocol Items: Recommendations for Interventional Trials (SPIRIT) figure. SPIRIT figure for the MEDACIS trial

### Study setting

The study is performed in Region Zealand of Denmark, and patients will be recruited from three cardiology departments (Department of Cardiology at Holbaek Hospital, Roskilde Hospital and Koege Hospital in Region Zealand, Denmark) within the region. Roskilde Department of Cardiology has the function of performing coronary angiography (CAG) and, if necessary, percutaneous coronary intervention (PCI) in the region. A subset of the patients will have their CAG and PCI performed at the Department of Cardiology, Rigshospitalet, Copenhagen, Denmark, but will be admitted to their regional hospital afterwards. A list of recruiting sites can be found at www.clinicaltrial.gov with Identifier NCT02451293.

### Eligibility criteria

Inclusion criteriaPatients should be admitted to a coronary care unit for ACS [46], and should be enrolled at the latest 4 weeks after the primary ACSParticipants should be aged 18 years or olderNo sign of current depression on the Major Depression Inventory (MDI) used as a diagnostic tool at the point of enrollmentParticipants must sign an Informed Consent Form.Premenopausal women (defined as no menstruation during the last 12 months) should have a negative pregnancy test. Furthermore, women of reproductive age should use reliable birth control (intrauterine devices, hormonal contraceptives including oral pills, patches, vaginal rings, and injections) during the entire trial period

Exclusion criteriaKnown allergic reaction to melatoninOngoing or previous pharmacologically treated depression or bipolar disorderNo dementia as determined by a Mini Mental State Examination (MMSE) score <24 is allowedAt the point of inclusion no participation in other pharmacological intervention trials is allowedNo participants with a diagnosis of Rotor syndrome or Dubin-Johnson syndrome, epilepsy, sleep apnea syndrome, systemic lupus erythematosus (SLE), rheumatoid arthritis (RA) or multiple sclerosis are allowedSevere liver disease, defined as transaminases above three times normal levels, and severe kidney disease defined as an eGRF under 40 ml/minChronic hypnotic treatment previous to the ACSKnown sleep disorder (e.g., insomnia, restless legs, etc.)Work involving nightshiftsDaily alcohol consumption above 5 units of alcohol (1 unit = 12 g alcohol)Predictable poor compliance (not speaking fluent Danish)Pregnant or breastfeeding womenSevere, life-threatening medical condition that implies that the patient cannot participate in the study course (e.g., cancer, stroke)Indication for coronary artery bypass graft (CABG)

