### Interventions

Patients will receive either 25 mg exogenous melatonin (intervention group) or matching placebo (control group) in an orally administered pill. Regarding the active substance each pill will contain 12.5 mg melatonin, and the placebo pill will be comparable to study medication except for the active substance. The medication will be packaged in blister packs consisting of 30 pills in each, and a total of seven blister packages will be packaged in a cardboard box (total of 210 pills). Patients will be instructed to take two pills (daily dose of 25 mg active substance) approximately 1 h before bedtime during the entire length of the study (12 weeks). Medicine compliance will be investigated at weeks 2 and 12 at clinical visits. All study medication will be produced by PharmaNord Aps. (Vejle, Denmark) in accordance with Good Manufacturing Procedure (GMP). The study medication will be shipped to the Region Zealand Hospital Pharmacy which will handle the randomization process.

If a participant withdraws their consent, they will leave the study. In the unlikely event that a female participant should become pregnant despite using reliable birth control, she will leave the study. Patients who have a recurrence of ACS during the study will be withdrawn from the study. In case of severe medical emergency (e.g., stroke or severe sepsis) requiring emergency surgery, stay in an intensive care unit, or more than 1 week of hospitalization will result in exclusion from the study. Diagnosis of a cancer during the study period will also result in withdrawal from the study. No further data will be collected from patients after leaving. However, previously collected data will be part of the final data analysis. No change in dose of study medication will be possible during the trial.

A medicine compliance of a minimum of 75% (pill count) at the clinical visits at weeks 2 and 12 are required. If the patients do not comply with these demands at either visit, they will be excluded from the study. Exclusion from the study entails stopping the study medication, and patient’s data will not be part of a per-protocol analysis. In case of medicine compliance at the first clinical visit, the data collected until this point will be part of a per-protocol analysis.

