### Primary outcome

The MDI is a self-rating scale with 12 questions. It has been extensively used in a Danish population [47] and is also thoroughly validated [48]. The questions cover the ten ICD-10 symptoms for depression, which are identical to the *Diagnostic and Statistical Manual of Mental Disorders, 4th edition* (DSM-IV) major depression diagnostic criteria except for one symptom, low self-esteem (question 4), which in DSM-IV is incorporated into a question about guilt (question 5).

The MDI holds a double function. It can be used as a diagnostic tool which, via an algorithm, can be transformed into the DSM-IV or ICD-10 categories of “mild,” “moderate,” or “severe” depression. The tool has been found to have satisfactory sensitivity and specificity with regard to the diagnosis of depression according to both the ICD-10 and DSM-IV [49]. The MDI can also be used as a rating scale, which can grade the severity of depression and this has been found to have an acceptable correlation with the Hamilton Depression Scale (HAM-D) [48].

For the purpose of the current study, the MDI will be used as a diagnostic tool at baseline with regard to the eligibility (inclusion/exclusion criteria) of the participants. Mild depression excludes participation and, as a diagnostic tool, mild depression is the presence of two core symptoms and two accompanying symptoms of depression. During the study, the MDI will be used as a rating scale to evaluate the severity and development of depressive symptoms. As a rating scale, a total MDI score (0–50 points) of 21 to 25 points corresponds to a mild depression, of 26 to 30 a moderate depression and above 31 points constitutes a severe depression. Incident depressive symptoms, defined as MDI score ≥21 any time after baseline MDI, is the primary outcome assessed using the MDI as a rating scale. Timing of outcome assessment can be seen in the SPIRIT figure (Fig. 3).

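### The pregnancy-test criterion defines premenopausal women by a condition that describes postmenopausal women

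*Protocol article*

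**What the plan says.** The protocol article, under Eligibility criteria, sets a pregnancy-test rule among the inclusion criteria: "Premenopausal women (defined as no menstruation during the last 12 months) should have a negative pregnancy test". The sentence that follows adds a contraception rule for a differently named group, which it does not define: "women of reproductive age should use reliable birth control". The accepted methods include "hormonal contraceptives including oral pills, patches, vaginal rings, and injections". The exclusion criteria in the same section bar women who are pregnant or breastfeeding. Under Interventions, the article says what happens if pregnancy occurs during the trial: "In the unlikely event that a female participant should become pregnant despite using reliable birth control, she will leave the study".

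**The concern.** A bracketed definition in an eligibility criterion tells site staff how to decide who falls under the rule. Here it describes the opposite of the group named. Staff who apply the bracket would test women who have had no periods for a year and would not test women who still have them, which is the group where an unrecognised pregnancy is possible.

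This is a safety rule that the article states wrongly, not a detail left to a fuller document. The criterion has a purpose in this trial: entry is open to adults from 18 years, participants take 25 mg of melatonin daily for 12 weeks, and the article treats pregnancy as a reason both for exclusion and for leaving the study.

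**Working it through.** No figure in the plan depends on this sentence, so the check is textual.

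**Step 1: the definition against the term.** The term is *premenopausal*. The condition in the bracket is absence of menstruation for 12 months, which is the usual marker of the postmenopausal state. The two do not fit together.

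**Step 2: who is tested under each reading.**

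| Woman | If the noun governs | If the bracket governs | If the word *no* is simply deleted |
|---|---|---|---|
| Menstruated within the past 12 months | tested | not tested | tested |
| Postmenopausal, no menstruation for 12 months | not tested | tested | not tested |
| Not postmenopausal, but no menstruation for 12 months because of hormonal contraception | tested | tested | not tested |

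The first two rows show the reversal. If both the noun and the bracket had to be met, only the third row would be tested, and menstruating women would still be left out.

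The third row matters for the repair. The article accepts hormonal methods, and some users of these do not menstruate yet can become pregnant after stopping. Deleting the negation would correct the first two rows and lose the third.

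**Step 3: is it corrected elsewhere?** In the available text *premenopausal*, *menstruation* and *pregnancy test* each occur once, all in this sentence. Pregnancy is mentioned two more times, in the exclusion criterion and in the rule for leaving the study. Neither names a test or says who is to be tested. The birth-control sentence uses a different, undefined term and so cannot repair the definition.

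**Step 4: effect on the design.** None. The calculated 116 per group and the planned 120 per arm rest on assumed event proportions of 31% and 15.5%, and the criterion does not enter that calculation. The article gives no age or sex distribution, so the number of women affected cannot be estimated.

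**The case against.** The strongest reply is that the sentence contradicts itself without clearly assigning the test to the wrong women. The noun still names the right group, and most readers would follow it. Separate rules also hold whichever way the bracket is read: pregnant women are ineligible, women of reproductive age must use birth control throughout, and a participant who becomes pregnant leaves. Only the question of who is tested is garbled.

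The reply also points to timing. Recruitment was under way when the article was written, with 150 of 240 patients included, so sites were presumably working from other documents, and nothing shows that any woman went untested. Finally, the clause about other causes of absent menstruation goes beyond reversing the slip.

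Much of this stands, and it is why the point is minor. It does not make the sentence correct. The exclusion of pregnant women says who may not enter, whereas the test is the only means named in the text for finding a pregnancy the woman does not know about. At the reported status, 240 − 150 = 90 patients remained to be enrolled, and the Recruitment section allows centres to be added, so a check of the working documents was still useful. The extra clause does go further than the minimal correction, but the article's own list of accepted contraceptives gives the reason for it.

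**Conclusion.** The definition is reversed as written, and the available text does not correct it. The point is minor: it is a wording error in an eligibility and safety rule, its intended meaning can be recovered, and it has no effect on sample size, endpoint, randomization or analysis.

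The conclusion rests on the ordinary meaning of the two terms and on the text available. The SPIRIT figure and the full operational protocol were not available and may carry the correct wording. No claim is made that any test was omitted or that any pregnant woman was enrolled.

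**What to change.** Replace the sentence with:

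> Women who are not postmenopausal need a negative pregnancy test. Postmenopausal means at least 12 months without menstruation and with no other cause for its absence, such as hormonal contraception.

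Leave the birth-control sentence as it stands. Check the operational protocol and the site documents for the same error and correct it if found. The cost is one corrected sentence and one document check. No calculation or analysis has to be redone.

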### Interventions

Patients will receive either 25 mg exogenous melatonin (intervention group) or matching placebo (control group) in an orally administered pill. Regarding the active substance each pill will contain 12.5 mg melatonin, and the placebo pill will be comparable to study medication except for the active substance. The medication will be packaged in blister packs consisting of 30 pills in each, and a total of seven blister packages will be packaged in a cardboard box (total of 210 pills). Patients will be instructed to take two pills (daily dose of 25 mg active substance) approximately 1 h before bedtime during the entire length of the study (12 weeks). Medicine compliance will be investigated at weeks 2 and 12 at clinical visits. All study medication will be produced by PharmaNord Aps. (Vejle, Denmark) in accordance with Good Manufacturing Procedure (GMP). The study medication will be shipped to the Region Zealand Hospital Pharmacy which will handle the randomization process.

If a participant withdraws their consent, they will leave the study. In the unlikely event that a female participant should become pregnant despite using reliable birth control, she will leave the study. Patients who have a recurrence of ACS during the study will be withdrawn from the study. In case of severe medical emergency (e.g., stroke or severe sepsis) requiring emergency surgery, stay in an intensive care unit, or more than 1 week of hospitalization will result in exclusion from the study. Diagnosis of a cancer during the study period will also result in withdrawal from the study. No further data will be collected from patients after leaving. However, previously collected data will be part of the final data analysis. No change in dose of study medication will be possible during the trial.

A medicine compliance of a minimum of 75% (pill count) at the clinical visits at weeks 2 and 12 are required. If the patients do not comply with these demands at either visit, they will be excluded from the study. Exclusion from the study entails stopping the study medication, and patient’s data will not be part of a per-protocol analysis. In case of medicine compliance at the first clinical visit, the data collected until this point will be part of a per-protocol analysis.

If a patient is diagnosed with a moderate-to-severe depression on the MDI during the study, they will be referred to a psychiatrist in training attached to the study (who is blinded to the allocated treatment). The psychiatrist in training will perform a structured clinical interview (Hamilton Depression Scale) with the purpose of diagnosing depression and its severity according to the *International Classification of Diseases, version 10* (ICD-10) criteria. Patients with a moderate-or-severe depressive episode according to the Hamilton Depression Scale and clinical assessment will be withdrawn from the study and offered open treatment for depression via the patient’s general practitioner (GP). All outcome data collected until the eventual termination in the study will be part of the final analysis. If the patient is diagnosed with a mild depression on the MDI, they will be allowed to continue in the study. The patient will be monitored using the MDI and phone calls according to the study protocol. In case of symptom progression on the MDI into moderate to severe depression, the participant will be referred to the psychiatrist in training as described above.

Patients will be contacted by phone seven times (every 2 weeks) during the trial to assure compliance and to promote their retention during follow-up. The patients will be reminded to fill in the relevant study questionnaires, reminded to take study medication, and monitored for occurrence of any adverse reactions, or changes in other medication since last contact with study investigators.

The participants are allowed to participate in all offered concomitant care at their regional cardiology department (e.g., cardiac rehabilitation). Startup of any medical antidepressant treatment in the trial period is prohibited and will lead to exclusion from the trial.

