### Exploratory outcomes

The pattern of participants leaving the study before completion of the 12-week period will be investigated. The different reasons for leaving the study (e.g., withdrawal of consent, medicine compliance, recurrent ACS, etc.) will be compared between the two groups. Furthermore, the timing of dropout between the two groups will be compared.

Safety and potential side effects will be closely monitored during the entire trial and reported in the proceeding publication. For specifics, see the “Harms and adverse events” section.

The Hospital Anxiety and Depression Scale (HADS) was originally developed by Zigmond and Snaith in 1978 [50] with the purpose of developing an easy-to-use tool for screening for mood disorders in a hospital setting. In a cardiac setting HADS-D has been shown to have adequate internal consistency, reliability and construct validity [51].

Actigraphy is a noninvasive method used to objectively evaluate a patient’s sleep and circadian rhythm. An actigraph (Octagonal Basic Motionlogger, Ambulatory Monitoring Inc., Ardsley, NY, USA), which is a wrist-worn minicomputer, will be mounted on the participant’s nondominant wrist at enrollment and worn for 2–3 weeks until the first clinical visit. Actigraphy has been shown to have a high validity and accuracy compared to polysomnography (PSG), the “gold standard” of sleep evaluation [52]. Actigraphy has been used extensively in patients undergoing surgery [53] and in cancer patients [54] but has not been investigated thoroughly in post-ACS patients [20].

Subjective sleep outcomes will be evaluated using a sleep diary, visual analog scales (VAS), and the Pittsburgh Sleep Quality Index (PSQI). A sleep diary is the patient’s own account of sleep data, and the patient is asked to fill in a diary page each morning after awakening. Visual analog scales regarding sleep will also be assessed on the scale ranging from “best conceivable sleep” at 0 mm to “worst conceivable sleep” at 100 mm. Furthermore, patients will fill out VAS on general wellbeing, fatigue, pain and anxiety. Lastly, the patients will fill out the PSQI, which assesses sleep quality during the prior 4 weeks and has a clinically established cutoff of ≥5 as being a poor sleeper and ≥8 as having sleep problems needing treatment [55].

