### Data collection

Data are collected in participant-specific Case Report Forms (CRFs) and will be stored for a 5-year period after study termination. As standard, an electronic CRF (eCRF) will be used to collect all study data from each participant throughout the study. The eCRF is created using the online platform Easytrial.net (Easytrial ApS, Glostrup, Denmark) which serves as the electronic data storage of the clinical trial. The individual questionnaires are sent to the individual participants via email with a unique generated link. In case a participant is noncompliant with the electronic setup (i.e., no Internet connection), they will fill out study questionnaires in paper format and the data will be transferred manually to the online study database. At the point of inclusion, baseline demographics will be collected from the patient and the patient record.

As previously described, phone calls and electronic (e.g., email) reminders will be sent out to assure participant retention and reduce loss to follow-up. No additional data are to be collected if a participant discontinues study medication or in other ways does not comply with the intervention protocols.

Using the eCRF implies that answered questionnaires are source data and are transferred directly to the electronic database upon completion. The sleep diary and the VAS administered for the initial 2 weeks are in paper format, and will later be transferred to the electronic database using double data entry. The study will be performed in accordance with Good Clinical Practice (GCP) and monitored by the GCP Unit from the University of Copenhagen. After completion of the trial the sponsor/investigator (first author) will have access to the final trial dataset.

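### The rule that ends data collection when a patient leaves or stops medication has no exception for safety data, so harms capture to week 12 is incomplete and conflicts with the promise of monitoring throughout the trial

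*Protocol article*

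**What the plan says.** The Interventions section lists the ways a patient leaves: withdrawn consent, pregnancy, recurrent ACS, a severe medical emergency, a cancer diagnosis, or pill-count compliance below 75% at week 2 or week 12. Several are themselves safety events:

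- Recurrent ACS: "Patients who have a recurrence of ACS during the study will be withdrawn from the study".
- New cancer: "Diagnosis of a cancer during the study period will also result in withdrawal from the study".
- Severe emergencies that need an urgent operation are covered too, and the text goes on: "stay in an intensive care unit, or more than 1 week of hospitalization will result in exclusion from the study".

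The consequence is then stated without qualification: "No further data will be collected from patients after leaving". The next sentence protects what came before: "However, previously collected data will be part of the final data analysis".

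Data collection repeats the rule and widens it to stopping treatment for any reason: "No additional data are to be collected if a participant discontinues study medication or in other ways does not comply with the intervention protocols".

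Against this, Exploratory outcomes says: "Safety and potential side effects will be closely monitored during the entire trial". The same section says that reasons for leaving and the timing of dropout will be compared between groups. Harms and adverse events describes how harms are collected: interviews at clinical visits and phone calls, plus the patient-rated UKU scale. It describes no contact after a patient has left.

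**The concern.** Read together, these sections stop the harms record when a patient leaves or comes off study medication. That group includes patients with serious events and those who stopped because of side effects. Two kinds of information are lost: how a serious event developed and ended, and any new harm between discontinuation and week 12.

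Safety is listed as an exploratory outcome, but it carries much of the trial's rationale. The abstract and the Discussion prefer melatonin to an SSRI because of its low toxicity, and the Discussion asks that a preventive treatment have few side effects. An incomplete harms record weakens that part of the answer.

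The issue is separate from missing MDI scores. Restoring MDI follow-up alone would not supply adverse-event outcomes.

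**Working it through.** **The plan's own figures.** The article gives no adverse-event rate, leaving rate or harms power, so there is no harms figure to reproduce. Its sample size of 116 per group (31% against 15.5%, two-sided 5%, power 80%) reproduces exactly with the pooled-variance normal approximation and is unaffected by this point.

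**Reach of the rule.**

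| Information | Under the text as written |
|---|---|
| Event that triggers leaving | Kept; it precedes leaving, and reasons are compared by arm |
| Side effects reported before leaving, including at the week-2 visit | Kept |
| Course and outcome of a serious event after leaving | Not collected |
| New harms from discontinuation to week 12 | Not collected |

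**Lost observation.** Follow-up is 12 weeks (Methods/design). A patient excluded at week 2 contributes 2/12 = 16.7% of planned harms observation. A patient excluded at the week-12 pill count loses none.

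**Could leaving differ by arm?** Interventions withdraws patients with confirmed moderate or severe depression. Sample size assumes 31% on placebo and 15.5% on melatonin develop depressive symptoms. Assume half of these are withdrawn, on average at week 6:

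- Placebo: 1 − 0.31 × 0.5 × 6/12 = 92.3% of planned observation.
- Melatonin: 1 − 0.155 × 0.5 × 6/12 = 96.1%.

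Intolerance could push the other way, so the net direction is unknown.

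**Effect on a comparison of proportions (all values assumed).** Let the true 12-week risk of an adverse event be r = 0.10 in both arms with constant hazard, a fraction d leave at week t, and nothing be recorded afterwards. The observed risk is (1 − d)r + d[1 − (1 − r)^(t/12)].

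For t = 2, 1 − 0.9^(2/12) = 0.0174:

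- d = 10%: 0.09 + 0.0017 = 0.0917
- d = 20%: 0.08 + 0.0035 = 0.0835
- d = 30%: 0.07 + 0.0052 = 0.0752

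| Leaving, melatonin v placebo | Observed RR, week 2 | Observed RR, week 6 |
|---|---|---|
| 10% v 10% | 1.00 | 1.00 |
| 20% v 10% | 0.91 | 0.95 |
| 30% v 10% | 0.82 | 0.90 |
| 10% v 30% | 1.22 | 1.11 |

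The true RR is 1.00 in every row. With r = 0.20 the ratios are nearly the same. Even with equal leaving, both risks are understated: 9.2% (week 2) or 9.5% (week 6) instead of 10%.

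**If leavers are at higher risk (assumed).** Suppose the hazard h = −ln(0.9)/12 is multiplied by k after leaving at week 2. The true risk is (1 − d)(0.10) + d[1 − exp(−2h − 10kh)].

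- k = 2, 20% v 10% leaving: 0.1151/0.1076, true RR 1.07, observed 0.91.
- k = 3, 30% v 10% leaving: 0.1435/0.1145, true RR 1.25, observed 0.82.

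A time-at-risk denominator does not recover this. All observed person-time in both arms has hazard h, so the rate ratio would be 1.00 while the true risk ratio is 1.07 to 1.25. It would correct the earlier table, where leaving is unrelated to harm risk.

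**The case against.** **The article is condensed.** No sentence says that adverse-event reporting stops at withdrawal. The Data collection sentence sits among text on reminders and retention, and the full protocol may contain a follow-up rule for serious events. The article also refers to GCP conduct and monitoring, and provides for unblinding in a SUSAR. This stands as a caution: the reach of the rule to safety data is a reading of unqualified text. But the article does not merely omit a detail. It states the rule twice, without exception, and describes no harms collection outside scheduled contacts.

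**No contradiction is needed.** Monitoring for the entire trial could mean for as long as the patient takes part. That reading is possible, and the text should say so if it is meant.

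**The lost time is off drug.** Exclusion entails stopping study medication, so later events are weaker evidence about melatonin, and a time-at-risk denominator handles purely unequal observation. Both points stand in part. They are reasons to separate on-treatment from post-treatment events, and they do not supply the outcome of an event that began on treatment.

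**Stronger readings a reader might infer.**

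- *Serious events are lost altogether.* They are not: the triggering event is kept and reasons for leaving are compared by arm.
- *Side-effect rates describe mainly patients who tolerated the drug.* This does not follow: the week-2 visit asks about side effects by list and by open question and uses the UKU scale, and those data are kept.
- *Stroke or sepsis always ends participation.* The text ties exclusion to emergency surgery, intensive care or more than a week in hospital.
- *The harms comparison is biased.* The documents give no leaving rates, and with equal leaving and equal hazard the ratio is undistorted.

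**Conclusion.** The point holds in a limited form. The no-data rule in Interventions and Data collection carries no safety exception and must be reconciled with the monitoring promised in Exploratory outcomes. Followed literally, it leaves harms capture incomplete: later course and outcome of serious events, and new harms to week 12, are missing for everyone who leaves or stops early, up to 10 of 12 weeks for a week-2 exclusion.

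Bias between arms is conditional on leaving that differs by arm or is related to harm risk, and its direction is unknown. The illustrative observed risk ratios of 0.82 to 1.22 for a true 1.00 rest wholly on assumed risks and leaving fractions. The conclusion also assumes that the full protocol does not already except safety data; if it does, only the article's wording needs correcting. This is worth fixing, but it does not affect the primary outcome or the sample size.

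**What to change.** Add one exception to Interventions and to Data collection: the rule does not apply to safety data. Unless the patient withdraws consent to further contact, adverse events continue to be recorded at the two-weekly calls to week 12, and serious adverse events and any pregnancy are followed to a recorded outcome.

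Report harms for all randomised patients who took study medication, with time at risk, and show on-treatment and post-treatment events separately.

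The cost is a short amendment and some extra calls to patients who have stopped; the call schedule already exists. Status of the trial reports 150 of 240 included, so 90 patients were still to be enrolled. Data on earlier leavers cannot be recovered, and the dataset will contain two follow-up regimes. The date and nature of the change should therefore be reported with the harms results.
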